#### Description and justification of route of administration and dosage

Administration of the study intervention via the intravenous (vs the oral or enteral) route is the most feasible in critically ill patients—a population where gastrointestinal dysfunction is prevalent and haloperidol absorption (ie, bioavailability) could be compromised. The dose of haloperidol or placebo equivalent to be used in the study is based on the following consideration: (1) Pharmacokinetics/pharmacodynamics; (2) efficacy; (3) safety. A (pilot) study in Erasmus Medical Centre (n=14 critically ill patients, abstract presented at European Society of Intensive Care Medicine 2016) showed no adverse events (eg, no QTc >500 ms), low serum levels (1.5–2.2 µg/L) and no clear relation between serum level and delirium resolution with haloperidol dosages up to 2 mg intravenously q8h (or: 3×2 mg intravenously). A feasibility trial of haloperidol for ICU delirium (MIND trial^8^) that used an average total daily dosage of 15 mg orally found higher serum levels (IQR 2.85–5.8 µg/L). No differences were found in QTc prolongation between treatment groups and placebo in this trial. None of these trials demonstrated clinically important safety concerns associated with haloperidol administration. Finally, a recently published trial of haloperidol for ICU delirium using haloperidol/placebo 10 mg intravenously q12h did not report any safety issues, using a QTc cut-off for safety of 550 ms, which may be regarded an indirect signal that such dosages are feasible and safe.^28^ The maximum dose of haloperidol of up to 5 mg intravenously q8h was further chosen because a previous Dutch guideline advocating the use of haloperidol recommended an intravenous haloperidol treatment dose of up to 20 mg/24-hour period.^29^ In our protocol, we chose q8h dosing (titrated up to 15 mg daily) given the greater potential susceptibility of critically ill adults to the side effects of haloperidol and the fact that this dosage is in line with existing haloperidol delirium protocols in several of the participating ICUs.

#### Patient assessments

Rigidity will be monitored with the Simpson-Angus scale^15^ and the Barnes Akathisia Rating Scale^30^ (see ‘Secondary study endpoints’ section) for study purposes only. The QTc interval will be measured daily before the administration of the second daily (afternoon) dose using a 12-lead EKG. When the QTc interval is found to be prolonged (>500 ms or an increase from baseline (=at randomisation) of ≥60 ms^31 32^), all non-study medications having the potential to prolong the QTc will be held if clinically feasible. A Standard Operating Procedure (SOP) lists the drugs known to prolong the QTc. Eight hours later, if QTc prolongation persists, study medication will be held or tapered according to the SOP and only resumed when the EKGs (evaluation frequency increased to q8h in this situation) reveal QTc prolongation to have dissipated.

#### General medical management at participating ICUs

In the six original participating ICUs, institutional delirium guidelines, based on the 2013 PAD guidelines and a Dutch ICU delirium guideline, were rigorously implemented over a 3-year period (2012 to 2015).^6 33 34^ During the inclusion period of the current trial, spot-checks will be performed by members of the investigative team at each centre to confirm delirium screening accuracy as a quality-of-assessments measure, and these will be documented in a qualitative manner.

#### Preparation and labelling of investigational medicinal product

Preparation and labelling will be done by the trial pharmacist (‘Apotheek A15’) according to Good Manufacturing Practices guidelines. Apotheek A15 is certified for these procedures. Trial medication will be dispensed to the pharmacies of the trial sites by the Hospital Pharmacy of Erasmus MC. See online supplemental appendix 5 for a description of the drug accountability.

10.1136/bmjopen-2019-036735.supp5Supplementary data

#### Escape medication

Knowing that half the subjects will be administered placebo, we anticipate two issues may affect the clinical management of enrolled patients: (1) agitation and (2) hallucinations.

Agitation management will be based on the following principles: (1) treat pain first with opioids; (2) use alpha-2 agonist for agitation that either persists or is not caused by pain; (3) GABA agonists (eg, benzodiazepines or propofol) are discouraged, but can be used on a short-term basis for the treatment of severe agitation (RASS ≥2) that cannot be effectively managed by other means.

Hallucination management will be based on the following principles: (1) pharmacological treatment may be withheld if the patient indicates they are not in distress; (2) for a patient in distress, a low-dose atypical antipsychotic (eg, quetiapine 12.5 mg q8h) may be administered on a short-term basis until the distress resolves.

Because of the pragmatic design of this trial, within these boundaries, the treatment and dose of escape medication is left to the treating physician since these are part of routine practice. However, before start of randomisation, these management principles for agitation and hallucination will be thoroughly implemented first with the help of detailed SOP’s to enhance uniformity in participating centres. Adherence to escape medication regimens will be closely monitored. Open-label haloperidol administration is strongly discouraged during the trial but can be used if the ICU team considers it necessary for acute breakthrough delirium symptoms that cannot be managed within the management boundaries outlined previously. Open-label haloperidol will be documented.

### Randomisation, blinding and treatment allocation

Legal representatives of eligible patients (when the patient is sedated or otherwise temporarily unable to consent) or the patient himself/herself will be asked for informed consent shortly after admission when the patient has no delirium or as soon as possible after admission when the patient already has delirium. Online supplemental appendix 6 contains an example of the patient consent form. In this study, the presence of delirium will be considered to be confirmed when the bedside nurse deemed the patient to have delirium based on assessment with the ICDSC or CAM-ICU, given the previous large-scale implementation project.^33^

10.1136/bmjopen-2019-036735.supp6Supplementary data

Delirious patients who fulfil all inclusion but no exclusion criteria, and for whom written informed consent has been obtained (as recorded in medical file), will be randomised. Randomisation coordination and start of a new case record form (CRF) will be guided by the electronic data capture (EDC) system of ALEA, constructed by the Clinical Trial Centre of the Erasmus Medical Centre and calibrated with the coordinating (Erasmus MC) and local pharmacies. We will randomise the recruited patients using a block design of eight patients in one block, and one block is assigned to a centre. We will have eight batches (numbered 1 through 8) of treatment and placebo, with four batches of placebo and four treatment (haloperidol). Each block will have a random assignment of eight batch numbers, having four placebo and four haloperidol patients included (a combination of 1 to 4 and 5 to 8 in random order). After eight patients are included in the study (ie, a block is full), a new block will be assigned to a centre.

On randomisation, the study drug with the corresponding randomisation kit numbers 1–8 (based on eight medication batches consisting of either haloperidol or placebo) will be obtained from the hospital pharmacy of each participating ICU. Each box from a batch/kit contains 10 ampules (5 mg/1 mL) of haloperidol or placebo. If all ampules are used, a new box from the same medication kit number with 10 ampules will be used. Study drugs are administered on prescription in the electronic patient data management system (PDMS) and are double-checked by ICU nurses before administration, which is similar to regular practice. Furthermore, the kit number was noted on randomisation in the medical file and the kit number could be retrieved at any time from the PDMS after first prescription on randomisation.

Blinding of the medication will be performed by the pharmacy, based on a randomisation list that will be generated electronically through a randomisation module in the EDC system of ALEA. Randomisation will be stratified per study centre (ie, equal number of patients in both study groups; see ‘Statistical analysis’ section). Only the involved pharmacists and the trial statistician are aware of the contents of each medication kit. Only the local (site) pharmacists are able to unblind study treatment of a patient in case of an emergency. Except for the hospital’s pharmacist responsible for the randomisation list, all other involved personnel with the study, caregivers, patients or their representatives will remain unaware of the treatment groups until the time of Database Lock. The unblinding procedure is specified in online supplemental appendix 7.

10.1136/bmjopen-2019-036735.supp7Supplementary data

Follow-up procedures will be performed according to designated SOPs. When possible and preferred by patients or families, questionnaires will be sent or visits planned at home when possible, for example, for incapacitated participants.

### Withdrawal of individual subjects

Subjects can leave the study at any time for any reason if they wish to do so without any consequences. The investigator can decide to withdraw a subject from the study for urgent medical reasons.

### Follow-up of subjects withdrawn from treatment

Data of withdrawn patients will remain in the database for statistical analysis purposes but will not be subject to follow-up. When patients specifically withdraw their consent for usage of their data, these data will be removed from the database and excluded from all analyses.

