### Premature termination of the study

The sponsor may decide to terminate the study prematurely based on the following criteria:

There is evidence of an unacceptable risk for study patients (ie, safety issue).There is reason to conclude that continuation of the study cannot serve a scientific purpose following confirmation of the Data Safety Monitoring Board (DSMB).The DSMB recommends to end the trial based on viable arguments other than described above.

The following stopping rules have been determined by the DSMB and have been laid down in a DSMB charter:

Early stopping of one individual participant, for example, to clear benefit or harm of a treatment or the occurrence of serious adverse reactions or events in one patient. In this case, de-blinding of this single patient may be necessary.Stopping of the trial as a whole to clear benefit or harm of a treatment or the occurrence of serious adverse reactions or events. As a result, further patient enrolment will be stopped. De-blinding may be necessary for all patients.

Reasons to stop the study include

Advice to do so from DSMB.Interim analysis shows a significant benefit difference between the treatment groups which will not be expected to change after inclusion of all subject as per the power analysis.

Suspected unexpected serious adverse reactions (SUSARs) are not expected due to the vast experience in clinical practice with the study drug (haloperidol).

If the study is terminated, the Medical Ethics Committees of all participating hospitals and the Central Committee on Research Involving Human Subjects (CCMO) will be notified.

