### Statistical analysis

### Primary and secondary study parameter(s)

Statistical analysis will be done according to intention-to-treat principle. All randomised participants will be included. The primary outcome is DCFDs, defined as the number of days in the first 14 days after randomisation during which the patient is alive without delirium and not in coma from any cause.^7^ Patients who are discharged before the 14-day study period has ended will be recorded as delirium and coma free after discharge.^8 35^ In addition, we will assume all patients who died within 14 days after randomisation to have 0 DCFDs.^7^ Differences between DCFDs between the haloperidol group and placebo group will be analysed using Poisson regression analysis, with adjustment for differences in baseline characteristics between treatment groups (when present) and for the different centres. We will collect data with regards to baseline demographics: age, sex, admission diagnosis category, APACHE II and APACHE IV, Sequential Organ Failure Assessment (SOFA) score, ICU days before study entry and pre-admission delirium duration in participants with delirium on admission. Pre-defined sub-analyses will include efficacy stratified by (1) agitated, mixed-type or hypoactive delirium; (2) the presence of hallucinations or delusions; (3) delirium severity (based on ICDSC score: low delirium severity=mean ICDSC score of 4 to 5; medium delirium severity=mean ICDSC score 5 to 7; high delirium severity=ICDSC score 7 to 8); and (4) sedation-related, hypoxic, metabolic or septic delirium. For cognitive and functional outcomes assessed with designated test batteries, non-parametric or parametric tests will be used depending on normality of scaled test results. Mortality risk will be assessed as a binary endpoint. A more detailed statistical analysis plan, to be drawn up before Data Base Lock, will be drafted for publication separately.

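### The rule ending follow-up for withdrawn patients also covers those withdrawn without any withdrawal of consent, which undermines the intention-to-treat analysis

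*Protocol article*

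**What the plan says.** The protocol article deals with withdrawal in two adjoining sections. *Withdrawal of individual subjects* concerns leaving the study. Subjects may leave whenever they wish, and in addition: "The investigator can decide to withdraw a subject from the study for urgent medical reasons".

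The next section carries the heading "Follow-up of subjects withdrawn from treatment", so it speaks of treatment and not of the study. Its rule is: "Data of withdrawn patients will remain in the database for statistical analysis purposes but will not be subject to follow-up". Withdrawal of consent to the use of data is a separate case, in which "these data will be removed from the database and excluded from all analyses".

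*Premature termination of the study* adds a stopping rule for single patients: "Early stopping of one individual participant, for example, to clear benefit or harm of a treatment or the occurrence of serious adverse reactions or events".

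The analysis section, *Primary and secondary study parameter(s)*, promises: "Statistical analysis will be done according to intention-to-treat principle. All randomised participants will be included". It says how to score patients discharged before day 14 (free of delirium and coma after discharge) and patients who die by day 14 (0 DCFDs).

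**The concern.** An intention-to-treat comparison needs outcomes from every randomised patient, whatever happened to the treatment. Here a patient can be taken out for a medical reason, having refused nothing, and the article then says that follow-up stops. Keeping the data gathered so far does not supply the rest of the 14-day primary outcome, vital status at 28 days and 1 year, or the 3- and 12-month assessments.

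The reasons named for such withdrawal are urgent medical reasons and, for individual stopping, benefit, harm or serious adverse reactions. These may well relate to prognosis, and some may relate to the drug. If so, the patients who drop out of sight differ from those who stay, and the two arms may lose different patients. A missing-data method in a later analysis plan can make assumptions about those outcomes but cannot observe them.

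**Working it through.** **1. What withdrawn can mean.**

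- *From treatment, as the heading says.* Stopping study drug would then end follow-up. The rest of the article does not work that way. *Dosages, dosage modifications and method of administration* stops the drug once delirium has resolved for 24 hours, while the primary outcome runs to day 14. Table 1 restricts only the EKG and the Simpson Angus Scale to days on study medication. *Adverse events* has several events assessed daily for 14 days after randomisation.
- *From the study, as the preceding section says.* The heading is then wrong, and the gap remains: a patient whom the investigator withdraws for urgent medical reasons is no longer followed, although no consent was withdrawn. On a natural reading the same applies to a patient stopped individually for harm or serious adverse reactions, though the article does not say so expressly.

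The text needs correction on either reading. The first sentence of the rule covers patients whose data may still be used, because withdrawal of consent to data use has its own sentence.

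**2. What is lost.** DCFDs after withdrawal, 28-day and 1-year mortality, and the 3- and 12-month outcomes. The scoring rules for early discharge and death also need events that may fall after withdrawal.

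**3. The plan's own sample size.** Inputs from *Sample size calculation*: difference 1 day (3.2 to 4.2), SD 4.2, power 90%, p<0.05. Two-sided testing is inferred, because a one-sided test would give 303 per arm.

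n per arm = 2 × (1.960 + 1.2816)² × 4.2² / 1² = 2 × 10.508 × 17.64 = 370.7, rounded up to 371; total 742.

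This matches the stated figure and shows that it contains no allowance for loss.

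**4. Power under loss.** The article gives no withdrawal rate, so the losses are assumed. Power = Φ(1 / (4.2 × √(2/n)) − 1.960), with n = 371 × (1 − loss):

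- no loss: Φ(3.243 − 1.960) = 90.0%
- 2%: 89.4%
- 5%: n = 352.45, Φ(3.161 − 1.960) = 88.5%
- 10%: 86.8%

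**5. Possible bias, if only followed patients are analysed.** Let w be the share of an arm that is lost, and g the shortfall in mean DCFDs of lost patients against followed patients. The followed mean exceeds the full-arm mean by w × g. With the same g in both arms, the treatment difference shifts by (w in haloperidol − w in placebo) × g. All values of w and g are assumptions:

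- difference in withdrawal 0: shift 0
- 5 percentage points, g = 2 days: 0.05 × 2 = 0.10 day
- 5 percentage points, g = 3 days: 0.05 × 3 = 0.15 day

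If more placebo patients are withdrawn, the sign reverses.

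The shortfall stops at 3 days because the planned placebo mean is only 3.2. Lost placebo patients would average 3.2 − (1 − w) × g. With w = 3% and g = 3 that is 3.2 − 2.91 = 0.29, which is possible. With w = 4% and g = 4 it is 3.2 − 3.84 = −0.64, which is not.

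**The case against.** The strongest reply is that the sections concern leaving the study under a loosely worded heading, and that the article already separates ordinary stopping of study drug from the end of assessment. That is largely right. A reader might infer that every patient taken off study drug is lost to follow-up; the dosing section, Table 1 and the adverse-event section show otherwise.

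A reader might also infer that haloperidol's known side effects drive the losses. The article does not support that step for its two most obvious examples. *Patient assessments* has study medication held or tapered, and later resumed, for QTc prolongation, and the dosing section has it lowered for rigidity. Neither is called withdrawal. The link to adverse effects rests on the urgent medical reasons and on individual stopping.

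Nor does the article support a bias in favour of haloperidol as a fact. Individual stopping may be for benefit as well as harm, and patients may leave for any reason in either arm.

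Finally, promising to analyse all randomised patients while some have incomplete follow-up is not a literal contradiction: the one fixes the analysis set, the other the data collected. Handling of missing data may be in the separate analysis plan, and follow-up procedures are referred to operating procedures that are not shown.

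These points limit the reach and the certainty of the concern. They do not remove the stated rule against follow-up for investigator-withdrawn patients who still consent, and an analysis plan cannot repair that.

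**Conclusion.** The concern holds in a limited form. The heading and the preceding section disagree on what is being withdrawn from, and the rule as written ends outcome collection for some patients who have not withdrawn consent. That undermines the intention-to-treat analysis and can bias the comparison if withdrawal relates to prognosis or treatment.

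The documents fix neither direction nor size. Under the assumptions shown, the shift in the primary comparison is 0 to 0.15 day, at most 15% of the 1-day target. It is zero under equal withdrawal only if the shortfall is also equal in both arms. The loss of power is small, about 1.5 percentage points at 5% loss. More patients would restore power but would not remove bias. For the 14-day ICU outcome the effect may be small; mortality and the 3- and 12-month outcomes are more exposed because more of their follow-up lies after any withdrawal.

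**What to change.** Reword the section, and align its heading with the one before it, so that discontinuing study drug or being withdrawn by the investigator for medical reasons ends treatment only. For every randomised patient, unless the patient or representative withdraws consent to follow-up:

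- continue to collect the delirium and coma scores already scheduled in the ICU, to day 14
- obtain vital status at 28 days and 1 year
- keep the patient eligible for the 3- and 12-month assessments on the same basis as other survivors.

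State whether individual stopping under *Premature termination of the study* falls under the same rule. Report withdrawals and data removals by arm. Keeping data already collected is the existing rule and needs no change. The rewording concerns data collection and leaves the decision to stop study drug as it is.

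The sample size stays at 742. The ICU scores are already scheduled three times a day, so they and vital status add little work. The later assessments cost more: neurocognitive testing takes 45 to 60 minutes per visit, and the article already limits it to about 400 survivors because of workload. At an assumed 5% withdrawal, about 0.05 × 400 = 20 of these would be withdrawn patients, with up to two test visits each.

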### Premature termination of the study

The sponsor may decide to terminate the study prematurely based on the following criteria:

There is evidence of an unacceptable risk for study patients (ie, safety issue).There is reason to conclude that continuation of the study cannot serve a scientific purpose following confirmation of the Data Safety Monitoring Board (DSMB).The DSMB recommends to end the trial based on viable arguments other than described above.

The following stopping rules have been determined by the DSMB and have been laid down in a DSMB charter:

Early stopping of one individual participant, for example, to clear benefit or harm of a treatment or the occurrence of serious adverse reactions or events in one patient. In this case, de-blinding of this single patient may be necessary.Stopping of the trial as a whole to clear benefit or harm of a treatment or the occurrence of serious adverse reactions or events. As a result, further patient enrolment will be stopped. De-blinding may be necessary for all patients.

Reasons to stop the study include

Advice to do so from DSMB.Interim analysis shows a significant benefit difference between the treatment groups which will not be expected to change after inclusion of all subject as per the power analysis.

Suspected unexpected serious adverse reactions (SUSARs) are not expected due to the vast experience in clinical practice with the study drug (haloperidol).

If the study is terminated, the Medical Ethics Committees of all participating hospitals and the Central Committee on Research Involving Human Subjects (CCMO) will be notified.

